#### Adverse events

Adverse events will be monitored, reported and handled appropriately. The risks imposed by this research project are deemed to be low, i.e., the burden of the experiments for the research subjects is limited. It is important to note that blood samples collected in the study are optional and not a criteria for participation. However, blood samples are taken by experienced nurses and a pain reducing cream is used to reduce any discomfort. Urinary samples are none invasive and thus cause no risk to the participants. In addition, the investigators have extensive experience conducting behavioral weight control studies, and active efforts will be taken by the research staff to ensure the participating families’ safety. Other adverse events may include psychosocial burden that parents may experience when made aware about their child’s weight status and the sense of guilt that may arise. To handle that, already in the first session of the ML program causes and consequences are reviewed in a non-judgmental way. Also, potential impact on the child’s self-esteem and the way to talk about body weight and obesity with children, if necessary, are addressed.

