### Statistical analysis

Intention-to-treat analysis using generalized linear mixed models with repeated measures will be used to examine the effects of the intervention on primary (aim 1) and secondary outcomes (aim 2) for the total study population (i.e., all three sites). The link function for the primary outcome (BMI z-score) will be the identity and the Gaussian family (equivalent to a linear regression). In secondary outcomes we will use a Gaussian identity and family link function for waist circumference, physical activity and sedentary behavior, and a logarithmic link and Poisson family function (equivalent to a Poisson regression) for child eating behavior and parental feeding practices. A random effect for country will be used to account for the clustered study design. In the models, we will control for relevant covariates such as sex, age, parental weight status, education level, income and foreign background. Random intercept and a random slope for time will be included in the model to control those non-observed confounders specific to each child that could be constant or vary in time, respectively. Furthermore, interactions between variables will be estimated. If missing values in the outcomes (primary and secondary) are more than 10%, these will be imputed through a two-part model (also known as a model for semi continuous data). In this model, we would simultaneously estimate the probability of not being missing (first part) and the outcome (second part), using a mixed generalized linear model, in which we would include, as explanatory variables: age, sex, parental weight status, foreign background, educational level, and the random effects which are aforementioned.

Statistical tests and analyses of the interaction of phenotypical outcomes with epigenetics will include Manhattan plots, volcano plots, principal component analysis (PCA)/cluster, heatmaps, partial least square-discriminant analysis (PLS-DA), correlations and association studies, linear regression models, receiver operating characteristic (ROC) curves and these will be implemented as appropriate.

The means and medians for the gut hormone values before and after the intervention will be compared, using Student’s t test and Mann-Whitney U test, respectively. The differences will be adjusted in a generalized linear mixed model, with an identity link and Gaussian family, including the confounders, both observed and unobserved, indicated above.

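### The imputation model for outcomes with more than 10% missing leaves out treatment arm, so it pulls the estimated effect toward zero

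*Protocol article*

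**What the plan says.** All of this is in the Statistical analysis section of the protocol article.

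- **Main analysis.** Intervention effects are estimated by intention to treat with a repeated-measures generalized linear mixed model, Gaussian with identity link for BMI z-score. Income is among the named covariates. Child effects enter as "Random intercept and a random slope for time will be included in the model", and for sites "A random effect for country will be used to account for the clustered study design".
- **Trigger.** "If missing values in the outcomes (primary and secondary) are more than 10" per cent, the values are imputed.
- **Method.** They "these will be imputed through a two-part model (also known as a model for semi continuous data"), in which "we would simultaneously estimate the probability of not being missing (first part) and the outcome (second part").
- **Predictors.** In that model "we would include, as explanatory variables: age, sex, parental weight status, foreign background, educational level, and the random effects which are aforementioned".

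The analysis covariates are introduced as examples. The imputation predictors are given as a complete list. The article does not say whether imputation is single or multiple, or whether the two parts share random effects.

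**The concern.** An imputation model must contain what the analysis model estimates. Here the analysis asks whether the arms differ, while the imputation model treats all children as one population. A missing intervention-arm value is then predicted toward the pooled mean, and so is a missing control value. The more values are filled in, the smaller the apparent difference. The rule covers the primary outcome and acts only when drop-out is appreciable. The trial is sized to detect 0.3 BMI z-score, so a real benefit of that size could be reported as clearly smaller.

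The named model class does not fit either. Two-part semicontinuous models describe an outcome with a mass of genuine values at one point, usually zero, plus a continuous part. A missing BMI z-score is a value nobody saw.

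**Working it through.** **Inputs from the article.** The design difference is 0.3 at 9 months (Sample size section). The target of 300 children at 1:1 gives 150 per arm. BMI z-score is measured at baseline, 10 weeks, 9, 15 and 21 months (Table 2). The plan has no figure of its own for the effect of imputation, so there is none to reproduce.

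**Assumptions (the article gives no SD, correlation or drop-out rate).** Random intercept SD 0.5; slope SD 0.025 per month; residual SD 0.25; true difference -0.15 at 10 weeks (2.3 months) and -0.30 from 9 months on; missingness random and equal by arm; variance components treated as known.

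**Step 1: covariance.** Cov(s,t) = 0.25 + 0.000625·s·t, plus 0.0625 when s = t. The baseline variance is 0.3125, the 9-month variance is 0.363 and their covariance is 0.25. The correlation is 0.25/√(0.3125 × 0.363) = 0.74.

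**Step 2: arm difference carried by an imputed value.** Without arm in the model, the 9-month value is predicted from the child's observed visits with best-linear-prediction weights. The arm difference that passes through, d, is the sum of weight × true difference at each observed visit.

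- Only baseline seen: 0.800 × 0 = 0.
- Baseline and 10 weeks seen: 0.543 × (-0.15) = -0.0815 (baseline contributes 0).
- Only the 9-month visit missed: 0.235 × (-0.15) + 0.235 × (-0.30) + 0.235 × (-0.30) = -0.176.

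**Step 3: expected estimate.** (1 - m)(-0.30) + m·d, with m the missing fraction. For example, at m = 0.20 with 10 weeks seen: -0.240 + 0.20 × (-0.0815) = -0.256.

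| Visits seen by children missing at 9 months | 20% missing | 30% missing |
|---|---|---|
| Baseline only | -0.240 | -0.210 |
| Baseline and 10 weeks | -0.256 | -0.234 |
| All except 9 months | -0.275 | -0.263 |

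**Step 4: coverage.** Simulation with 150 per arm, regressing the completed 9-month value on arm and baseline, gave reported SEs of 0.0423, 0.0431 and 0.0445 at 20% and 0.0398, 0.0411 and 0.0433 at 30% (same row order). Coverage ≈ Φ(1.96 - bias/SE) - Φ(-1.96 - bias/SE). For the first row at 20%: 0.060/0.0423 = 1.42, giving about 71%; simulated coverage was 70%. Simulated coverage by row was about 70, 82 and 91% at 20%, and about 38, 65 and 86% at 30%. Repeat runs of the first row ranged over 69–70% and 37–40%. Analysis of the observed values alone gave about -0.30 with about 95% coverage.

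**Step 5: type of imputation.** A simpler check used one follow-up visit, 75 per arm, an assumed SD of 0.6 and 20% missing. Without arm, the estimate was -0.241 (single predicted value), -0.238 (single random draw) and -0.240 (multiple imputation). The bias does not depend on the type. With arm added and multiple imputation, it was -0.302 and the SE matched the sampling SD (ratio 0.99).

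**The case against.** **The random effects rescue the plan.** In part they do. A child's intercept and slope carry arm information when post-baseline visits exist, which is why the last table row loses only about 8% at 20% missing. Other assumed variance components and 10-week effects give -0.25 to -0.29 at 20% and -0.23 to -0.29 at 30% for children seen at 10 weeks. Estimating the components from an arm-free fit also softens the loss slightly (-0.259 with 84% coverage, against -0.256, at 20%). For a child lost after baseline, nothing is recovered.

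**The error is conservative.** With arm-free single imputation, type I error stayed near 0.055 in the simpler check. The estimate is still wrong. Under arm-free multiple imputation, power was 0.67 at 20% missing, against 0.83 from the observed data.

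**The standard error.** A reader might infer that it is understated. The article does not support this. It states neither single nor multiple imputation, and a condensed article may leave that to a fuller document. In the 150-per-arm scenario with drop-out after 10 weeks, the reported SE equals the estimator's own sampling SD (0.043 and 0.043 at 20%), so the lost coverage comes from bias. With arm-free multiple imputation the SE is too large (0.104 against 0.085 in the simpler check).

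**Blood outcomes.** The Adverse events section notes that "blood samples collected in the study are optional and not a criteria for participation", and a reader might infer that hormone and epigenetic values would be imputed for children who gave no blood. The Statistical analysis section ties secondary outcomes to aim 2, which the Aim section limits to waist circumference, eating behavior, feeding practices and physical activity. Blood markers belong to aim 3.

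**The missingness part.** It would go too far to say that modelling the chance of being observed contributes nothing. The two parts are estimated together, and if their random effects are linked, this is a joint model that could address non-random missingness. The link is unspecified, not shown to be absent.

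**The 10% trigger.** It is prespecified, so its data dependence alone is not the fault.

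**Conclusion.** The point holds as a bias toward zero from an imputation model that is incompatible with the analysis it feeds. Followed as written, the rule loses about 8–20% of a true -0.30 at 20% missing (0.025/0.30 to 0.060/0.30) and about 12–30% at 30% missing (0.037/0.30 to 0.090/0.30), under the stated variance components. The upper end is the missing fraction itself and needs no variance assumption: it applies when baseline is the only other visit seen. Physical activity, measured only at baseline and 9 months in Table 2, is always in that position.

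The sizes rest on assumed variances, an assumed course of the effect, and equal random missingness in both arms. The direction follows from the predictor list for any real effect that the child's other visits do not fully reflect. The misapplied two-part label is a secondary fault. No claim is made about an understated standard error or about imputing blood outcomes.

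**What to change.** Remove the 10% rule from the primary analysis. State that the likelihood-based mixed model on all observed visits is primary at any missing rate. It already uses these data validly under missing-at-random.

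If imputation is kept, replace the two-part model with multiple imputation containing arm, visit, arm-by-visit, baseline and other observed outcome values, the random effects, and every analysis covariate including income. If a joint model of missingness and outcome is wanted, place it as a not-at-random sensitivity analysis, say how its two parts are linked, and drop the semicontinuous label.

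The cost is one reworded paragraph. No new data are needed, and the primary analysis becomes simpler than the one now described.

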**Methods/design:**

A two-arm, parallel design randomized controlled trial in 300 2-to 6-year-old children with overweight and obesity from Romania, Spain and Sweden (*n* = 100 from each). Following baseline assessments children are randomized into the intervention or control group in a 1:1 ratio. The intervention, the ML program, consists of 10-weekly group sessions which focus on evidence-based parenting practices, followed by the previously validated MINISTOP application for 6-months to support healthy eating and physical activity behaviors. The primary outcome is change in body mass index (BMI) z-score after 9-months and secondary outcomes include: waist circumference, eating behavior (Child Eating Behavior Questionnaire), parenting behavior (Comprehensive Feeding Practices Questionnaire), physical activity (ActiGraph wGT3x-BT), dietary patterns (based on metabolic markers from urine and 24 h dietary recalls), epigenetic and gut hormones (fasting blood samples), and the overall acceptance of the overweight and obesity management in young children (semi-structured interviews). Outcomes are measured at baseline and after: 10-weeks (only BMI z-score, waist circumference), 9-months (all outcomes), 15- and 21-months (all outcomes except physical activity, dietary patterns, epigenetics and gut hormones) post-baseline.

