## Methods

### Study design

ML Europe is a two-arm parallel design randomized controlled trial (RCT) comparing overweight and obesity treatments in 2-to 6-year-old children in three countries (Romania, Spain, and Sweden). Following baseline assessments, participants will be randomized into the intervention and control group in a 1:1 ratio. The intervention group receives a 10-week parent support program (the ML program) which focuses on evidence-based parenting practices [7, 30] followed by a previously validated 6-month mHealth program (the MINISTOP app, PI: [name]) to support healthy lifestyle changes [17, 18]. The control group receives standard treatment as offered in the country of participation. The different interventions are described in greater detail below. Assessments will be conducted at 10 weeks, 9 months, 15 months, and 21 months post-baseline (see Fig. 1 for study outline). This study protocol follows the SPIRIT 2013 statement [31, 32].

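### Gut hormones: the Mann-Whitney U test does not fit paired before-after values, and the text states no comparison between the randomised arms

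*Protocol article*

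**What the plan says.** The trial is a two-arm parallel design in which "participants will be randomized into the intervention and control group in a 1:1 ratio" (Study design). Gut hormones come from fasting blood at baseline and 9 months only (Table 2). The abstract agrees: later visits cover "15- and 21-months (all outcomes except physical activity, dietary patterns, epigenetics and gut hormones) post-baseline". Blood sampling is optional (Adverse events).

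The Statistical analysis section gives gut hormones two sentences. The first sets the crude comparison: "The means and medians for the gut hormone values before and after the intervention will be compared". It assigns Student's t test to the means and the Mann-Whitney U test to the medians. The second sets the adjusted one: "The differences will be adjusted in a generalized linear mixed model, with an identity link and Gaussian family, including the confounders, both observed and unobserved". Those confounders are the ones named earlier in the section, where the text says: "Random intercept and a random slope for time will be included in the model to control those non-observed confounders specific to each child".

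Neither sentence mentions the intervention or control arm.

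**The concern.** There are two separate problems in the text as written.

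- **The test.** Before and after values from one child are correlated. The Mann-Whitney U test treats its two samples as independent and has no paired form. It is also not, in general, a test of medians, which is the role the sentence gives it.
- **The contrast.** A before-after comparison does not use the randomisation. Children aged 2 to 6 grow for nine months between the samples, and they were selected for overweight or obesity. Growth and regression to the mean can shift the values in both arms without any effect of the programme.

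The second problem matters more. A wrong crude test wastes information from a sample that may already be small, whereas a missing arm contrast leaves a randomised trial with a gut-hormone result that cannot be attributed to the intervention.

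**Working it through.** The article states no figure for the gut-hormone analysis, so there is none to reproduce. The check sets the statements side by side and then sizes the two problems under stated assumptions.

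**1. Are the values paired?** Yes. Table 2 marks gut hormones at baseline and 9 months in the same children, so a child sampled twice contributes one pair.

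**2. Do the named tests fit?** Mann-Whitney does not fit a before-after contrast. Student's t test has a paired and an unpaired form, and the text does not say which. Naming it beside Mann-Whitney rather than the Wilcoxon signed-rank test suggests the unpaired form but does not settle it.

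**3. Does another sentence supply the arm comparison?** The intention-to-treat mixed model that examines intervention effects is tied to aims 1 and 2. Gut hormones are under aim 3 (Aim) and are not among the outcomes given a family and link there. The general remark that interactions will be estimated does not specify arm by time. By contrast, the urine profiles do get an explicit comparison between study groups.

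**4. Cost of ignoring the pairing (crude step only).** Assumptions: equal variances at both times, within-child correlation ρ (not in the article), two-sided nominal 5%. For n pairs with variance σ², the variance of the mean difference is 2σ²(1−ρ)/n, but an unpaired test uses 2σ²/n.

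- Standard-error ratio, unpaired to paired: r = 1/√(1−ρ)
- True size: 2 × [1 − Φ(1.96 r)]
- Power where the paired test has 80% (noncentrality 2.80): Φ(2.80 − 1.96 r)

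| ρ | r | True size | Power |
|---|---|---|---|
| 0.3 | 1.20 | 1.9% | 68% |
| 0.5 | 1.41 | 0.6% | 51% |
| 0.7 | 1.83 | 0.03% | 22% |

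For ρ = 0.5: 1.96 × 1.414 = 2.77, so size = 2 × [1 − Φ(2.77)] = 0.6%, and power = Φ(2.80 − 2.77) = Φ(0.03) = 51%.

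The table applies to means. A simulation (4,000 runs, normal data, 75 pairs, shift of 0.3 SD) also covers Mann-Whitney. At ρ = 0.5, power was 0.42 for the unpaired t test and 0.40 for Mann-Whitney, against 0.73 for the paired t test and 0.70 for the signed-rank test. With no shift, both unpaired tests rejected in 0.6% of runs. The 75 pairs are illustrative, because the number of children who give blood twice is unknown.

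**5. Cost of a before-after contrast.** Assume no treatment effect, a shift of 0.3 SD over time in both arms, 75 children per arm and ρ = 0.5. The SD of change is √[2(1−0.5)] = 1, its standard error is 1/√75 = 0.115, and the noncentrality is 0.3/0.115 = 2.6. A correct paired test within one arm should then reject in roughly Φ(2.6 − 1.96) = Φ(0.64) = 74% of trials by the normal approximation. Simulation gave 72% (39% for Mann-Whitney). The between-arm comparison of change rejected in 4.5%, close to nominal. Correcting the test alone therefore does not solve the attribution problem; it detects the shared time shift more often.

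**The case against.** The strongest reply is that the crude tests are not the whole analysis. The next sentence adds a mixed model with observed and unobserved confounders, and earlier in the section the unobserved ones are handled by child-level random effects. If these carry over, the adjusted analysis respects the pairing. This stands: the figures in step 4 apply to the crude step only, and a reader should not infer that the plan ignores within-child correlation throughout. What the model does not clearly supply is the arm. It adjusts the same before-after differences and names no arm or arm-by-time term.

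A second reply is that the authors meant to compare the arms at baseline and again at 9 months, for which independent-samples tests would be right. The choice of Mann-Whitney gives this some support. It is possible, but it is not what the sentence says, and if it is the intention, the sentence still has to be rewritten.

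Other stronger readings are tempting and not supported:

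- That both tests are certainly unpaired. This is certain only for Mann-Whitney.
- That ignoring the pairing produces false positives. With positive correlation the error is conservative.
- That the authors will report a before-after change as a programme effect. The article nowhere says so. Aim 3 concerns mechanisms, the hypotheses claim no effect on gut hormones, and a within-child question is legitimate there. The abstract does, however, list gut hormones among the secondary outcomes of a randomised trial.
- That assay drift will bias the change. The article gives intra- and inter-assay variation only, with no sign of drift.

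Condensation for a journal does not answer the point: a specific test and a specific contrast are stated, and they do not match.

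**Conclusion.** The point holds in a limited form. Mann-Whitney is the wrong test for the before-after contrast named, the form of the t test is open, and the text states no randomised comparison for gut hormones. The missing arm contrast is the main fault; the test mismatch is secondary and costs power.

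The sizes are illustrative. They rest on assumed correlations of 0.3 to 0.7, normal data, equal variances and, in the simulations, a 0.3 SD shift and 75 pairs or 75 children per arm, none of which the article gives for gut hormones. The direction does not depend on the exact values: any positive correlation makes the unpaired test conservative, and any time trend shared by the arms contaminates a before-after contrast.

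The correction is worth making, but its reach is narrow: a mechanistic outcome under aim 3, measured on optional blood samples. The BMI z-score analysis is untouched.

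**What to change.** Rewrite the two gut-hormone sentences.

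- **Main analysis.** State the intervention-versus-control contrast at 9 months, estimated in the Gaussian mixed model already planned, on the log scale if the values are skewed. Include arm, time, arm by time, country and a child random intercept. This form can keep children with only one sample, which matters because blood is optional. The alternative is to model the 9-month value with baseline as a covariate, plus arm and country; each child then has one outcome record, so the child intercept drops out.
- **Random slope.** With two values per child, a random slope for time cannot be separated from residual variance, so say that the intercept alone is used for this outcome.
- **Within-arm change.** Report it as description only, with the paired t test or, in place of Mann-Whitney, the Wilcoxon signed-rank test.
- **If a comparison of arms at each visit was intended,** say so. The independent-samples tests can then stay as crude companions to the model.

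The cost is a few sentences of analysis text, with no new data, visits or samples.

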### Hypotheses

Our central hypothesis is that the intervention (the ML program followed by the MINISTOP app for boosting) will be more effective in decreasing children’s BMI z-score (primary outcome), improving eating and feeding behaviors, and physical activity (secondary outcomes) compared to standard care. Another study hypothesis is that the intervention will produce changes in urinary metabolites, which will serve as biomarkers of the nutritional outcomes or as targets for application. We also hypothesize that the parent program and the mHealth intervention will be well accepted by families and caregivers.

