### Measures

Outcome measures are collected at baseline, 10 weeks, 9 months, 15 months, and 21 months post baseline. Table 2 presents when outcome measures are assessed and the instruments used to assess child and parental behaviors are displayed in Table 3.

**Table 2 Tab2:** Socio-demographic characteristics and outcome measures collected at different time points

Outcomes	Measure	Baseline	10 weeks	9 months	15 months	21 months
Child						
Weight and height (BMI z-score)	Measured by health care professionals	x	x	x	x	x
Waist circumference		x	x	x	x	x
Date of birth	Child background questionnaire	x				
Country of birth		x				
Sex		x				
Health status		x		x	x	x
Family structure		x		x	x	x
Daycare		x		x	x	x
Visits to health care regarding weight		x		x	x	x
Screen time		x		x	x	x
Breakfast consumption		x		x	x	x
Sugar sweetened drinks consumption		x		x	x	x
Eating behavior	Child Eating Behavior Questionnaire	x		x	x	x
Physical activity / sedentary behavior	ActiGraph wGT3x-BT accelerometer	x		x		
Food intake	Urine samples, 24 h dietary recall	x		x		
Gut hormones	Fasting blood samples	x		x		
Epigenetic markers	Fasting blood samples	x		x		
Parent						
Weight and height (BMI)	Parent background questionnaire	x		x	x	x
Date of birth		x				
Country of birth		x				
Sex		x				
Education level		x				
Health status		x		x	x	x
Occupation status		x		x	x	x
Income		x		x	x	x
Social and economic support from network		x		x	x	x
Perceived level of comfortable life		x		x	x	x
Parenting behavior	Comprehensive Feeding Practices Questionnaire	x		x	x	x

Abbreviations: *BMI* body mass index

**Table 3 Tab3:** Measures used in the study

Instrument, reference	Domains	No. items	Description
Child Eating Behavior Questionnaire (CEBQ),		35	
Wardle et al. 2001 [45]	*Food approach*		
	Food responsiveness	5	The child’s general appetite
	Enjoyment of food	4	The child’s interest in food
	Emotional overeating	4	If the child eats as a response to emotions
	Desire to drink	3	The child’s desire to drink
	*Food avoidance*		
	Satiety responsiveness	5	If the child gets full easily or not
	Slowness in eating	4	The child’s speed of eating
	Emotional undereating	4	If the child eats less in response to emotions
	Fussiness	6	The child eats a limited variety of food
Comprehensive Feeding Practices Questionnaire (CFPQ),		49	
Musher-Eizenman & Holub 2007 [46]	Monitoring	4	Parents keep track of child’s intake of less healthy foods
	Emotional regulation	3	Parents use food to regulate the child’s emotional stress

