##### Metabolites of food intake

First void urinary samples will be collected from the children and will be used to assess metabolites of food intake. Two urine samples from the child will be collected by the parents at home six and 3 days before the visit to the research group. The third urine sample is collected on the morning of the visit to the research group. The urine metabolite analysis will be carried out as previously described [29]. In brief, urine samples will be measured by proton nuclear magnetic resonance (^1^H-NMR) spectroscopy. Global urinary ^1^H-NMR profiles will be used to predict the quality of the diet using the World Health Organization guidelines as a reference. Individual urinary metabolites associated with the intake of foods will be used to assess the dietary profile of the child. The Dietary Metabotype Score that embodies concentrations of urinary metabolites related to food components and adherence to diet will be developed and validated against one 24-h dietary recall with a parent. The 24-h recall will cover the day before the visit to the research group. For children attending preschool a food diary for teachers to fill out will be collected to cover the food intake not provided by the parent.

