For the validation of child food intake with metabolic markers in urine, the urinary dietary model will be derived using previously described methodology [29]. Comparison between the study groups will be carried out using PCA and Monte Carlo cross-validated partial least square-discriminant analysis (MCCV-PLS-DA) methodology. The relationship between dietary biomarkers and the dietary metabolite profile will be carried out using a generalized linear mixed model, with an identity link and Gaussian family, including, again, the confounders.

The semi-structured interviews with parents and health care professional will be fully transcribed verbatim and analyzed using thematic analysis [57].

For our analyses we will use R [35], STATA version 12.1 (StataCorp 2011, College Station, TX, USA) and SPSS Statistics (IBM, Armonk, NY, USA).

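### The only stated between-arm urine analysis is a classification (PCA and MCCV-PLS-DA) that gives no effect estimate and is not tied to the baseline samples or to the child as unit

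*Protocol article*

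**What the plan says.** Under Hypotheses, the article expects that "the intervention will produce changes in urinary metabolites", which is a statement about an effect of the intervention.

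Under Metabolites of food intake, each assessment has three first-void samples: "Two urine samples from the child will be collected by the parents at home six and 3 days before the visit to the research group", and "The third urine sample is collected on the morning of the visit to the research group". Table 2 (Measures) marks the row "Urine samples, 24 h dietary recall" at baseline and 9 months only. The Abstract agrees on the later visits: "15- and 21-months (all outcomes except physical activity, dietary patterns, epigenetics and gut hormones) post-baseline". A child can therefore give 3 × 2 = 6 samples.

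Under Statistical analysis, the comparison of arms for urine is one sentence: "Comparison between the study groups will be carried out using PCA and Monte Carlo cross-validated partial least square-discriminant analysis (MCCV-PLS-DA) methodology". The next sentence brings in a mixed model, but for another question: "The relationship between dietary biomarkers and the dietary metabolite profile will be carried out using a generalized linear mixed model". The intention-to-treat repeated-measures model earlier in that section, with its child and country random effects, is stated for aims 1 and 2. Urine belongs to aim 4.

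**The concern.** PCA ignores the arm labels and displays the main directions of variation. PLS-DA looks for a direction that separates the arms, and Monte Carlo cross-validation reports how well that direction classifies held-out profiles. Neither, as named, says by how much the intervention moved a metabolite or a diet score, or with what uncertainty. The stated hypothesis would then be judged on a classification result alone.

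Two features of the design are also left unconnected to this comparison. Each child has a baseline measurement, which could remove stable differences between children. Each child also has three samples per visit, which are correlated and need to be averaged or kept together. Elsewhere the same section does connect design and analysis: gut hormones, measured at the same two visits, are compared before and after the intervention, and the differences are adjusted in a mixed model with observed and unobserved confounders. The urine comparison between arms has no such step.

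At stake are an interpretable result for this hypothesis, some precision and, under one possible implementation, a misleading cross-validated separation.

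**Working it through.** **No figure to reproduce.** The article states no power, sample size or error rate for the urine comparison. The check is on coverage, precision and cross-validation.

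**Step 1: is an arm difference in urine estimated anywhere?**
- Repeated-measures model: aims 1 and 2. Aim 2 lists waist circumference, child eating behaviour, parental feeding practices and physical activity. The link functions given for secondary outcomes do not mention urine.
- Mixed model in the urine paragraph: relates dietary biomarkers to the metabolite profile, not arm to outcome.
- PCA and MCCV-PLS-DA: the only item that compares arms.

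So no arm difference with a confidence interval is stated.

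**Step 2: what the baseline samples are worth.**
Inputs: 3 samples per visit and 2 visits (documents); within-child correlation ρ of one metabolite, assumed 0.2 to 0.5 (not in the documents); child effect assumed stable over 9 months.

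Correlation between the baseline and 9-month three-sample means: r = ρ / (ρ + (1 − ρ)/3).
- ρ = 0.2: 0.2 / (0.2 + 0.267) = 0.43
- ρ = 0.5: 0.5 / (0.5 + 0.167) = 0.75

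Variance of the arm effect relative to a 9-month-only comparison:

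| | Formula | ρ = 0.2 | ρ = 0.5 |
|---|---|---|---|
| Baseline-adjusted | 1 − r² | 0.82 | 0.44 |
| Change score | 2(1 − r) | 1.14 | 0.50 |

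Baseline adjustment always helps or is neutral under these formulas. A change score helps only when r exceeds 0.5, that is when ρ > (1 − ρ)/3, or ρ > 0.25. If the child effect drifts over 9 months, r is smaller and both gains shrink.

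**Step 3: what three samples per child can do to cross-validation.**
Null simulation with no arm difference: 1:1 arms, 3 samples per child at one visit, 2-component PLS-DA, 30 random splits with 30% held out, 12 data sets per setting. Correlation (0.2, 0.5) and number of variables (50, 200, 500, taken as independent) are assumed. An honest AUC is 0.5.

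300 children, mean cross-validated AUC:

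| ρ | Variables | Split by sample | Split by child | One mean profile per child |
|---|---|---|---|---|
| 0.2 | 50 | 0.54 | 0.50 | 0.49 |
| 0.2 | 200 | 0.57 | 0.49 | 0.49 |
| 0.2 | 500 | 0.62 | 0.50 | 0.49 |
| 0.5 | 50 | 0.59 | 0.51 | 0.51 |
| 0.5 | 200 | 0.67 | 0.49 | 0.48 |
| 0.5 | 500 | 0.77 | 0.49 | 0.48 |

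With 150 children, splitting by sample gives 0.57 to 0.86, against 0.49 to 0.54 by child. The inflation comes from the split and disappears when a child's samples stay together or are averaged.

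The univariate analogue is the design effect 1 + (3 − 1)ρ, which is 1.4 or 2.0. A test that took the three samples as independent would have a two-sided error rate of about 0.10 (ρ = 0.2) or 0.17 (ρ = 0.5) instead of 0.05.

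**The case against.** The strongest reply is that this is a condensed article. The input matrix, the handling of replicates and the unit of resampling commonly go into an analysis plan, and the article points to previously described methodology for its urine work. PLS-DA can be run on change profiles, on averaged samples or with splits by child. The urine paragraph opens as a validation of food intake, and nothing makes the arm comparison confirmatory.

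Most of that stands, and it rules out several stronger readings that a reader might infer:
- *That baseline samples are dropped, or that each sample is treated as an independent unit.* The article says neither; it is silent.
- *That the method cannot show the hypothesised change.* With randomised arms, a difference at 9 months is a valid sign of an intervention effect. Leaving out baseline costs precision, not validity.
- *That the analysis will show separation where there is none.* This needs splitting by sample, which is not stated. The AUCs above 0.5 in the table describe a possible implementation, not the plan, and depend on assumed correlations and variable counts.

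A further objection is that the Dietary Metabotype Score, the natural single outcome, is still to be developed and validated in this trial. That is a fair caution. It is met by deriving the score without use of arm labels and by reporting named metabolites beside it.

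What the reply does not remove is the choice of method. Using a classification as the sole between-arm comparison for a hypothesis about an intervention effect is stated in this document, not left open.

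**Conclusion.** The point holds in a limited form. The stated urine comparison gives no effect size or confidence interval and is not linked to the baseline samples or to the child as unit, although the data for both are already planned.

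Its size on precision: baseline adjustment gives 0.82 to 0.44 of the variance of a 9-month-only comparison. This rests on an assumed within-child correlation of 0.2 to 0.5 and a child effect that is stable over 9 months. Its size on false separation is nil if each child's samples are kept together or averaged. With 300 children it is an AUC of about 0.54 to 0.77 under the null only if samples are split at random. These figures show direction and range and are no forecast for this trial.

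Severity is minor. The aim is secondary and largely exploratory, and the primary outcome is not affected.

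**What to change.** Add to Statistical analysis, as the randomised urine comparison, the between-arm difference at 9 months with a confidence interval, in the Dietary Metabotype Score (derived without use of arm labels) and in a short list of named metabolites. Average the three samples per child per visit, and adjust for the child's baseline value and for country.

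Keep PCA and MCCV-PLS-DA as a supporting display, and state that all samples of a child stay in the same training or test set. Running it on change profiles is optional, because change can be less precise than 9-month values when the within-child correlation is low.

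The cost is a few lines of text and slightly more analysis work, with no new samples or visits. The downside is that children without baseline urine need a stated rule in the adjusted model.
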